## Abstract

**Background:**

Varicocele is a high incidence and is considered to be the most common and correctable cause of male infertility. Oxidative stress (OS) plays a central role in the pathogenesis of varicocele-related male infertility. In addition to varicocelectomy, antioxidant supplementation seems to be an effective scheme for the treatment of varicocele-related male infertility, but it is still controversial. The purpose of this study is to determine the effects of alpha-lipoic acid (ALA) supplementation on sperm quality in patients with varicocele-related male infertility.

**Methods:**

In this randomized controlled clinical trial, we will randomize 80 patients with varicocele-related male infertility from Guilin People’s Hospital. The non-surgical observation group (*n* = 20) will receive ALA, the non-surgical control group (*n* = 20) will receive vitamin E, the surgical observation group (*n* = 20) will receive ALA after the operation, and the surgical control group (*n* = 20) will receive vitamin E after the operation. The course of treatment will be 3 months. The results will compare the changes in semen parameters, sex hormones, testicular volume, sperm DNA fragment index (DFI), seminal plasma malondialdehyde (MDA), and total antioxidant capacity (TAC) between the groups at baseline and after 3 months of antioxidant supplementation.

**Discussion:**

Whether it is necessary to use antioxidants in varicocele-related male infertility, how potent antioxidants should be used, postoperative application or non-surgical independent application still needs to be explored. This study attempts to compare the effects of two antioxidants (ALA and vitamin E) on sperm quality in patients with varicocele-related male infertility (surgical or non-surgical) and attempted to answer the above questions.

**Trial registration:**

Chinese Clinical Trial Registry (ChiCTR) ChiCTR2100054958. Registered on 29 December 2021

## Administrative information

Note: The numbers in curly brackets in this protocol refer to the SPIRIT checklist item numbers. The order of the items has been modified to group similar items (see http://www.equator-network.org/reporting-guidelines/spirit-2013-statement-defining-standard-protocol-items-for-clinical-trials/).

## Introduction

### Background and rationale {6a}

It is estimated that about 8–12% of couples suffer from infertility, nearly half of which are mainly caused by male factors. The causes of male subfertility can be related to congenital, acquired, or idiopathic factors that impair spermatogenesis [1]. Among the acquired factors, varicocele is considered to be the most common and correctable cause of male infertility [2, 3]. The incidence of varicocele is estimated to be 35–44% in males with primary infertility and 45–81% in males with secondary infertility [4]. The etiology of varicocele is multifactorial, and its pathogenesis is unclear [5]; however, studies have shown that reactive oxygen species (ROS) and the resultant oxidative stress (OS) play a central role in the pathogenesis of varicocele-related male fertility and are the key pathophysiological factors of male fertility caused by varicocele [6]. Due to the presence of varicocele, problems such as elevated testicular temperature, hypoxia, and OS will ultimately lead to testicular damage and abnormal sperm quality [7–10].

Varicocelectomy repairs and reduces ROS caused by varicocele, improves sperm DNA integrity and sperm quality, and is a common treatment for varicocele-related male infertility [11–13]. A meta-analysis has confirmed that sperm DNA integrity in patients with clinical varicocele is significantly improved following varicocelectomy [14]. The meta-analysis also found that adjuvant medical therapy after varicocelectomy improved sperm quality and sperm DNA integrity more than no medical treatment after varicocelectomy [15]. Vitamins are mainly used as antioxidants in the treatment of varicocele in infertile men; the application of antioxidants such as vitamin C and vitamin E after varicocelectomy has a positive effect on semen parameters in patients with varicocele-related male infertility, and even the application of vitamins alone can improve semen quality in some patients with varicocele-related male infertility without surgical treatment [16–18]. However, new evidence suggests that antioxidant supplementation on operated or non-operated does not improve semen parameters and pregnancy rates with varicocele-related male infertility without prior screening for OS [19].

However, ROS generated by OS is undoubtedly an important pathogenic factor in the entire varicocele process, affecting spermatogenesis through multiple pathways and mechanisms [20]. Especially for infertility caused by moderate-to-severe varicocele, whether it is necessary to use antioxidants, how potent antioxidants should be used, postoperative application, or non-surgical independent application still needs to be explored. Alpha-lipoic acid (ALA), chemically named 1,2-dithiolane-3-pentanoic acid, is an 8-carbon, cyclic disulfide antioxidant with the formula C_8_H_14_O_2_S_2_ and molecular weight 206.33 g/mol, which represents a promising antioxidant in the field of female and male infertility that inhibits oxygen-free radicals and rejuvenates oxidized antioxidants (i.e., glutathione and vitamins C and E) [21], as well as promotes the function of enzymes with antioxidant function. Animal experimental studies have shown that ALA can reduce the negative side effects of elevated testicular temperature and reduce OS in varicose rats [22]. It has also been clinically confirmed that ALA or ALA compound antioxidants can improve sperm motility and reduce sperm DNA damage in patients with varicocele after surgery [23, 24]. However, what role does ALA play in varicocele-related male infertility, and can it improve sperm quality more than traditional antioxidants? This is also a problem we think about and try to solve to help us formulate a more optimized treatment plan for varicocele-related male infertility.

### Objectives {7}

The general objective is to determine the efficacy and significance of ALA in varicocele-related male infertility through a randomized controlled clinical trial.

The specific objective is to determine the effect of different intensities of antioxidant conservative and surgical treatment of varicocele on sperm quality of varicocele-related male infertility patients by comparing surgical and non-surgical supplementation of ALA or vitamin E.

### Trial design {8}

This is a single-center, randomized, controlled, non-commercial clinical superiority trial evaluating the effectiveness of alpha-lipoic acid on sperm quality in patients with varicocele-related male infertility. The eligible participants will be allocated randomly into the non-surgical observation group, non-surgical control group, surgical observation group, or surgical control group in a ratio of 1:1:1:1. The four groups will be intervened for 3 months and followed up for 6 months. The flow chart is shown in Fig 1.

**Fig. 1 Fig1:**
[figure not shown]
Flow chart describing the study protocol

## Methods: participants, interventions, and outcomes

### Study setting {9}

The trial will be conducted in Guilin People’s Hospital, Guilin, China.

### Eligibility criteria {10}

The inclusion criteria are as follows:Infertile male aged 23–50 yearsAbnormal semen qualitySpouse with normal fertility or suffering from infertility-related diseases, but may be curedPrimary varicocele, physical examination to diagnose varicocele grade II (palpable in the standing position) or grade III (visible without palpation), color Doppler ultrasound measurement of the spermatic vein diameter at rest (DR) ≥ 2.8mm, time of reflux (TR) ≥ 4 s during the Valsalva maneuver.

The exclusion criteria are as follows:Pituitary or testicular organic diseasesAzoospermia or chromosomal abnormalitiesHistory of vas deferens surgery or obstruction of the vas deferens cannot be ruled outReproductive system infectionSevere erectile dysfunction or ejaculation disorderSecondary varicocelePatients who have undergone varicocelectomyHistory of cancer, diabetes, or serious heart, liver, kidney, and hematopoietic diseasesSevere mental illnessParticipates in other clinical trials or uses drugs that improve sperm quality or affect varicocele within the past 3 monthsParticipants who have been using antioxidants or other nutritional supplements for a long time or within the past 3 months

### Who will take informed consent? {26a}

At baseline, the primary investigator will explain to patients the content and process of participating in the trial and obtain written informed consent upon enrollment.

### Additional consent provisions for collection and use of participant data and biological specimens {26b}

This trial involves collecting biological blood and semen samples. In the informed consent form, participants will be informed and asked if they consent to the use of their biological samples and data in future research.

### Interventions

#### Explanation for the choice of comparators {6b}

Vitamin E is an antioxidant commonly used in male infertility and a widely used adjuvant drug for varicocele and after varicocelectomy.

#### Intervention description {11a}

In the four groups, the non-surgical observation group will take a lipoic acid capsule 0.6 g, once a day; the non-surgical control group will take a vitamin E soft capsule 100 mg, twice a day; the surgical observation group will take a lipoic acid capsule 0.6 g, once a day; the surgical control group will take an oral vitamin E soft capsule 100 mg, twice a day. The course of treatment will be 3 months.

#### Criteria for discontinuing or modifying allocated interventions {11b}

In case of significant adverse drug reactions, the intervention will be stopped and reported to the Medical Ethics Committee of Guilin People’s Hospital. If the participant asks to stop the intervention, the intervention will stop.

#### Strategies to improve adherence to interventions {11c}

Monthly follow-up and record adverse drug reactions. Research participants can contact the investigators by phone or WeChat at any time, feed back drug use and treatment, and obtain guidance or suggestions.

#### Relevant concomitant care permitted or prohibited during the trial {11d}

Supplementation with vitamin E or ALA will not require alteration to usual care pathways.

#### Provisions for post-trial care {30}

Although known relevant studies suggest that the risks associated with this trial are small, the patients will be followed for 6 months after intervention and will be provided with adjunctive and post-trial care according to standard medical practice irrespective, regardless of the trial itself.

### Outcomes {12}

The primary outcome is the change of semen parameters (mainly progressive motility sperm) compared between the study groups at baseline and after 3 months of oral medication. Semen samples will be collected in sterile containers by masturbation after 2–7 days of abstinence. A semen analysis will be performed within 60 min after ejaculation and liquefaction using semen quality analyzer, and the semen volume, PH, sperm concentration, total motion, progressive motility (PR), and normal morphology will be measured according to the WHO laboratory manual for the examination and processing of human semen (5th edition) [25].

As secondary outcomes, the following will be measured at baseline and after 3 months of treatment: (1) Sex hormones, including follicle-stimulating hormone (FSH), luteinizing hormone (LH), estradiol (E2), and testosterone (T), will be determined by electrochemiluminescence using fasting blood. (2) Testicular volume will be calculated using Lambert’s formula (length × height × width × 0.71) [26]. (3) Sperm DNA fragment index (DFI) will be detected by flow cytometry-assisted sperm chromatin structure analysis (SCSA), seminal plasma malondialdehyde (MDA) levels will be detected by means of the tiobarbituric acid method, and seminal plasma total antioxidant capacity (TAC) will be detected by ferric-reducing antioxidant power (FRAP) assay method. (4) The pregnancy rate will be assessed during the 6-month follow-up after the completion of the trial.

### Participant timeline {13}

The participant timeline is presented in Fig. 2.

**Fig. 2 Fig2:**
[figure not shown]
Data collection points

### Sample size {14}

Sample size estimation uses a completely random design to compare multiple sample means. The target sample size was estimated on PR sperm (as the primary outcome of this trial) using the PASS 2021 version 21.0.3 (NCSS, LLC, Kaysville, UT, USA). The number of samples considering the type I error *α* = 0.05 and the type II error *β* = 0.20 with 80% test power. According to a previous study [23], and a retrospective analysis of our data center in the past 2 years, changes in PR sperm mean value in the surgical observation group was 12.05, and the standard deviation was 3.96; changes in PR sperm mean value in the surgical control group was 6.56, and the standard deviation was 8.90; changes of PR sperm mean value in the non-surgical observation group was 4.15, and the standard deviation was 8.68; changes of PR sperm mean value in the non-surgical control group was 1.42, and the standard deviation was 7.60. After calculation, the sample size required for each group was 16 people. To reduce error, we slightly expanded the target sample size and estimated a dropout rate of 20%. The sample size will be practically 20 patients per group, and we will consider a total of 80.

### Recruitment {15}

Patients will be recruited from the outpatient department of Andrology and Urology of Guilin People’s Hospital.

### Assignment of interventions: allocation

#### Sequence generation {16a}

The allocation sequence will be generated by computer through the block randomization method, and the block length will be multiple and remain blind and will not be open to the subjects, researchers, and other relevant personnel participating in the trial. Qualified participants will be randomly divided into four groups at a ratio of 1:1:1:1.

#### Concealment mechanism {16b}

Allocation will be concealed in sequentially numbered, opaque, sealed envelopes containing the randomization assignments. After each participant meets the eligibility criteria and signs informed consent, the appropriate numbered, opaque, sealed envelope will be opened.

#### Implementation {16c}

The generation and allocation of sequences will be conducted by a designated researcher who is not involved in the data collection or analysis.

### Assignment of interventions: blinding

#### Who will be blinded {17a}

The grouping involves surgery, and non-surgery makes it impossible to blind the trial participants. However, the data collection staff, outcome assessors, and data analysts will be blinded. The varicocelectomy will be performed by the same surgeon and he will be blinded.

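### Surgery does not explain why ALA versus vitamin E is left open, and opening the full assignment at enrolment puts the surgeon's blind to drug at risk

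*Protocol article*

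**What the plan says.** Section {17a} (Who will be blinded) gives one reason for open participants: "The grouping involves surgery, and non-surgery makes it impossible to blind the trial participants". It then claims a blind for staff: "However, the data collection staff, outcome assessors, and data analysts will be blinded". On the operator it says: "The varicocelectomy will be performed by the same surgeon and he will be blinded". It does not say what the surgeon is blind to.

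Section {16b} (Concealment mechanism) fixes when the assignment is revealed: "After each participant meets the eligibility criteria and signs informed consent, the appropriate numbered, opaque, sealed envelope will be opened". Under {8} and {16a} that assignment is to one of four arms, so it carries both surgery and drug. The Methods part of the abstract has surgical men receive their antioxidant after the operation.

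Section {11a} describes two regimens that a man can tell apart. For ALA, "the non-surgical observation group will take a lipoic acid capsule 0.6 g, once a day". For vitamin E, "the non-surgical control group will take a vitamin E soft capsule 100 mg, twice a day". The surgical arms have the same two regimens. No dummy or matching product is described.

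Section {11c} plans monthly follow-up with recording of adverse drug reactions, and adds: "Research participants can contact the investigators by phone or WeChat at any time, feed back drug use and treatment, and obtain guidance or suggestions". Section {18b} plans telephone or WeChat follow-up during treatment and for 6 months after it. Section {18a} lists adverse events among the 3-month data and pregnancy among the 6-month data.

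**The concern.** The four arms combine two factors: surgery or not, and ALA or vitamin E. The reason in {17a} concerns the first factor only, yet it is used to leave both open. For the drug comparison within a surgical stratum the protocol gives no reason at all.

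Three things are at stake.

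- **Withdrawal before the operation.** A surgical man who already knows he has the familiar vitamin rather than the new product, or the reverse, can withdraw for that reason before he has received either treatment.
- **The surgeon.** Any blind he has can be broken if the drug is known to the patient or on file before he operates.
- **The reported blind.** A publication would claim blinded data collection staff, while adverse events and pregnancy are reported by men who know their drug.

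The reading of progressive motility by an analyser is not the weak point. Who returns for the 3-month sample, and what else he takes meanwhile, is less protected.

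**Working it through.** The blinding claim has no figure of its own, so the main check sets the sections side by side.

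**1. Does the stated reason cover the drug comparison?**
- Surgical ALA versus surgical vitamin E: both arms are operated on, so knowing that one was operated on does not identify the drug.
- Non-surgical ALA versus non-surgical vitamin E: neither arm is operated on, and the same holds.
- Surgical versus non-surgical arms: the reason is correct.

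What does reveal the drug is the once-daily versus twice-daily regimen in {11a} without dummies. Section {17a} does not mention this.

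**2. When can the drug be known?** In surgical men the order is eligibility and consent, envelope opened ({16b}), operation, then drug (abstract, Methods). The drug assignment is thus available before an operation that does not need it. The protocol does not say who opens the envelope or when the man is told.

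**3. What can the surgeon be blind to?** He knows that he operates, so his blind can only concern ALA versus vitamin E. Under step 2 that information exists before surgery, and no section keeps it from him.

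**4. Which staff are exposed?**

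| Role or data | Contact with unmasked men | Position |
|---|---|---|
| Semen, hormone, DFI, MDA and TAC readers ({12}) | None needed | Largely protected |
| Analysts ({19}, coded data) | None needed | Largely protected |
| Recorders of adverse events and pregnancy ({11c}, {18a}, {18b}) | Direct | At risk |
| Sequence holder ({16c}) | Knows the arm; takes no part in data collection or analysis | Not claimed as blind |

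**5. Size, for illustration.** First, the plan's own figures in {14}. A four-group one-way ANOVA with the stated means, alpha 0.05 and the largest stated SD (8.90) as common SD gives 16 per group (power 0.826), and 16 / (1 − 0.20) = 20. The stated sample size reproduces, and this point does not change it.

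Progressive motility is measured only at baseline and 3 months ({18a}), and {20c} carries the last record forward. A man with no 3-month sample then contributes a change of zero. If k extra men of 20 are lost from one arm, unrelated to response, the arm's mean change falls by mean × k / 20. The surgical means are 12.05 (ALA) and 6.56 (vitamin E), a difference of 5.49.

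| Extra men lost, k (assumed) | Lost from vitamin E arm | Lost from ALA arm |
|---|---|---|
| 1 | 6.56 × 1/20 = 0.33 (6% of 5.49) | 12.05 × 1/20 = 0.60 (11%) |
| 2 | 0.66 (12%) | 1.21 (22%) |
| 4 | 1.31 (24%) | 2.41 (44%) |

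Extra losses on vitamin E widen the difference and extra losses on ALA narrow it. The plan expects 20% × 20 = 4 losses per arm, so k = 4 means doubling the loss in one arm only.

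**The case against.** The specific objective in {7} also compares surgical with non-surgical treatment, and for that contrast the reason in {17a} is correct. Participant-open treatment with laboratory endpoints is a legitimate design. Both points stand. Neither supplies a reason for leaving the drug open within a stratum.

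A reader might infer more than the documents support:

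- **That drug-use reports undo the surgeon's blind.** They cannot. Such reports begin after the operation. Only the early opening of the envelope could expose the surgeon.
- **That the staff blind is broken.** Section {11c} names the investigators, not the blinded roles. The article may simply not describe a separation that exists in practice. This is a risk for those who record adverse events and pregnancy, and it does not extend to assay readers or to analysts using coded data.
- **That all 40 surgical men know their drug before the operation.** This is an inference from {16b}. The section says when the envelope is opened, not who is told.
- **That coded opaque containers would mask the drug.** They would not, because the number of daily doses identifies the arm.

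**Conclusion.** The point holds in a limited form. The rationale in {17a} is wrong for the drug comparison. The drug assignment is disclosed earlier than the design needs, and the surgeon's blind is neither defined nor protected. For data collection staff there is a risk and no demonstrated breach.

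The documents do not give the size of any bias. The shifts of 6% to 44% of the planned surgical difference rest on assumed differential losses of 1 to 4 men in one arm, on loss unrelated to response, and on last record carried forward. They show what the mechanism could do, not what it will do. This is a cheap improvement to the plan and not a flaw that invalidates the primary outcome.

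**What to change.** 1. **Two-part envelope ({16b}).** The outer part gives surgery or no surgery. The inner part gives the drug and is opened only at first dispensing, which in surgical men is after the operation. The sequence, the 1:1:1:1 ratio and the regimens stay as they are. Withdrawal before the operation can then no longer depend on the drug. Withdrawal after dispensing still can, and non-surgical men gain little.
2. **Restate {17a}.** Participants are open to surgery. Because the regimens visibly differ and no dummies are used, they are also effectively open to drug once it is dispensed. The surgeon is blinded to drug only. Do not claim masking through coded containers.
3. **Separate the contacts ({11c}, {18b}).** Existing investigators who do not collect or assess the blinded outcomes take the drug-use and adverse-reaction contacts. The sequence holder in {16c} should not take them, because that would make the holder a data collector, contrary to that section. Claim staff blinding only for the semen, hormone, testicular volume and assay outcomes and for the analysis, not for adverse events or pregnancy.

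The cost is slightly more envelope and dispensing work, some reassignment of calls among existing staff, and a narrower blinding claim. No placebo is needed.

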#### Procedure for unblinding if needed {17b}

Not applicable.

### Data collection and management

#### Plans for assessment and collection of outcomes {18a}

Data will be collected at three time points: (T0) pre-treatment (baseline) records—baseline parameters, sperm quality, sex hormones, testicular volume, sperm DFI, seminal plasma MDA, and TAC; (T2) 3 months post-treatment—sperm quality, sex hormones, testicular volume, DFI, seminal plasma MDA and TAC, and adverse event; and (T3) 6 months post-treatment—pregnancy rate.

